### Participants

Ethical approval has been granted by University of Southampton Research Ethics Committee (ERGO ID: 92317). Eligibility criteria for inclusion are: (i) aged 18–50 years; (ii) normal or corrected to normal vision; and (iii) fluency in the English language. Exclusion criteria are: (i) diagnosis of any type of chronic pain or psychiatric condition; (ii) currently experiencing pain; or (iii) diagnosis or knowledge of any reading difficulties. Participants will be recruited using social media, word-of-mouth, and the website SONA which is used to recruit undergraduate psychology students at the University of Southampton. BSc Psychology students at the University of Southampton will receive partial course credit for participating. A power analysis was conducted using G*Power [82] to determine suitable sample size for an ANOVA, with a medium effect size based on the pilot study which revealed many of the intensity and unpleasantness ratings between benign and pain modification groups were of medium to large effect (effect size *f* =  0.244, α error probability =  0.05, power (1 – *β* error probability) =  0.80, numerator degrees of freedom =  1, and number of groups =  2). This indicates a sample size of 134 is required for these conditions to be met. The start date for this study is 1^st^ June 2024 and the planned end date as registered with the University of Southampton Research Ethics Committee is 1^st^ May 2026.

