#### Interpretation of somatosensory sensations assessment.

In addition to ambiguous heat stimuli discussed previously, the main experimental study will also assess interpretation of ambiguous cold stimuli administered to the non-dominant hand using the TSA-II. Specifically, cold stimuli at 60%, 80%, 100%, 120% and 140% of an individual’s cold pain threshold will be presented three times each, in a random order set across participants. Percentage threshold temperature values exceeding the safety limits of the TSA-II will be capped at 0°C (i.e., the TSA-II’s safety limits). Each cold trial will begin with the thermal stimulus decreasing from baseline temperature at a rate of 1°C/second until reaching the target temperature. The target temperature will be held for three seconds before returning to baseline at a rate of 8°C/second. At this point, participants will rate via pen and paper visual analogue scales the intensity (from 0 no sensation to 100 most intense pain you can imagine), and the unpleasantness (from 0 not unpleasant at all to 100 extremely unpleasant) of the stimulus. The fifteen cold trials will be presented consecutively with a 10 second inter-trial interval. The order of heat and cold pain trials will be randomised across participants, with the thermode removed for three minutes between each block of trials. This task will take approximately 20 minutes to complete

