### Data reduction and analytic plan

Data will be analysed using SPSS for Windows 29. For all analyses the significance level will be set to *p* = .05 and two-tailed. Standardized procedures will be followed for identifying and handling missing data and outliers [85]. Visual inspection and descriptive statistics will be performed to identify missing data, and should they exist missing data analysis performed. If <  10% of data is missing and the data is missing at random or completely at random, multiple imputation by chained equations will be used [86,87]. Datasets will be inspected for outliers using box and whisker plots inspect for univariate outliers, and Mahalanobis distance (*D*^*2*^) to detect multivariate outliers [85]. Should outliers exist, their cause will first be established, and if resulting from unique cases or data anomaly, will either be removed or transformed (e.g., log transformation, square root transformation) as appropriate prior to final analysis of the dataset [85].

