Descriptive statistics will be computed for demographic characteristics, self-report measures (scored according to their instructions), cognitive bias task scores (Ambiguous Scenarios Task test phase, Sentence Generation Task, Visual-Probe Task and free recall task) and responses on the Interpretation of Ambiguous Somatosensory Sensations Task. Differences between the benign and pain modification groups will be conducted using independent samples *t*-tests and mixed-design ANOVAs where appropriate. Should any statistically significant differences be observed between groups on demographic or self-report measures, analyses will be conducted controlling for these (e.g., Analysis of Covariance). Pearson’s correlation coefficients will be conducted between outcomes on the self-report measures, cognitive bias scores and interpretation of ambiguous sensations ratings. As thermal pain sensitivity is associated with age (e.g., [88–90]), Pearson’s correlation coefficients will also be computed between age and interpretation of ambiguous sensations ratings. Should these be statistically significant, then age will be controlled for as a covariate where appropriate in the statistical analyses. The moderating effects of visual imagery and intolerance of uncertainty on the association between group and interpretation bias scores from the Ambiguous Scenarios Task will be investigated using linear multiple regression models. Similarly, linear multiple regression models will be used to test the effect of group on interpretation bias measures while controlling for other variables that differ between groups.

Data from the Ambiguous Scenarios Task, Sentence Generation Task and ISSA will be processed as discussed above for the pilot study. The only difference is that for the Sentence Generation Task, two raters will independently and blindly categorise participant response sentences as either pain-related (e.g., *He had a pressing pain in his head*) or benign (e.g., *The boy was pressing the buttons in the lift*). The initial inter-rater agreement will be computed, and any disagreements between raters will be discussed in order to reach consensus (involving a third independent member of the research team if necessary).

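### The 10% and MAR/MCAR conditions on multiple imputation have no defined unit and no named fallback, and the plan's own device-limit exclusions can breach them

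*Protocol article*

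**What the plan says.** All references are to the protocol article; unless noted, they are to its main-study part.

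- **Data reduction and analytic plan, general statement.** "Standardized procedures will be followed for identifying and handling missing data and outliers". Then: "Visual inspection and descriptive statistics will be performed to identify missing data, and should they exist missing data analysis performed".
- **Same section, the rule.** "If < 10% of data is missing and the data is missing at random or completely at random, multiple imputation by chained equations will be" the method. No branch is written for 10% or more, or for data judged not missing at random.
- **Same section, group comparison.** "Differences between the benign and pain modification groups will be conducted using independent samples *t*-tests and mixed-design ANOVAs where appropriate". ANCOVA and multiple regression are named for covariate adjustment and moderation, not for missing data.
- **Exclusion of ratings.** The pilot analysis plan removes ISSA ratings when the required temperature was beyond the device's safety limits. The main-study plan says ISSA data will be processed as in the pilot, so the exclusion carries over.
- **Pilot, Task evaluations.** The 140% level was out of reach for five participants (3 benign, 2 pain) and the 120% level for two (1 and 1), at an upper limit of 50°C. The main-study limits are 53°C and 0°C, and a cold block is added.
- **Participants.** The sample size of 134 rests on "effect size *f* = 0.244", a 0.05 significance level and power of 0.80. No allowance for incomplete data is stated.

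**The concern.** The rule is written down, so this is not detail left to a separate analysis plan. It has three faults.

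1. **The unit is undefined.** The 10% could count participants with any gap, participants missing a given variable, participant-by-level cells or single ratings. These give different answers on the same data.
2. **The conditions do not track when imputation is valid.** Validity depends on the mechanism and the imputation model, not on a fixed percentage. Observed data can argue against MCAR, but they cannot separate MAR from MNAR. The choice of method therefore becomes a judgement made after the data are seen.
3. **There is no concrete fallback.** If a condition fails, the named group comparisons remain. A standard mixed-design ANOVA across stimulus levels needs every cell filled, so a participant without a valid 140% level would also lose the valid ratings at the other four heat levels.

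At stake are power for the two primary outcomes and who is analysed. Loss at the device limit falls on participants with high heat thresholds, so a listwise analysis describes the lower-threshold part of the sample.

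**Working it through.** **1. The plan's own sample size.** Two groups, numerator df 1, denominator df N − 2, noncentrality λ = N·f², with f² = 0.244² = 0.059536.

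- N = 134: λ = 134 × 0.059536 = 7.978, power 0.8006.
- N = 133: power 0.798.

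The smallest N reaching 0.80 is 134, so the stated figure reproduces.

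**2. Pilot losses under different denominators.** A participant who cannot reach 120% cannot reach 140% either, since that target is hotter. The two are therefore among the five.

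| Unit counted | Loss | Under 10%? |
|---|---|---|
| Participants with any empty heat cell | 5/18 = 27.8% | no |
| Participants missing the 140% variable | 5/18 = 27.8% (exact 95% CI 9.7 to 53.5%) | no |
| Participants missing the 120% variable | 2/18 = 11.1% (1.4 to 34.7%) | no |
| Heat participant-by-level cells | (5 + 2)/(18 × 5) = 7/90 = 7.8% | yes |
| Heat and cold cells, assuming no cold loss | 7/180 = 3.9% | yes |

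Each level is given three times, so counting single ratings gives the same 7.8%.

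**3. Power if incomplete participants are dropped.** Same formula with N reduced. The effect and its SD are taken as unchanged among those retained.

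| Loss | N analysed | λ | Power |
|---|---|---|---|
| 0 | 134 | 7.978 | 0.80 |
| 11.1% | 134 × 16/18 ≈ 119 | 7.085 | 0.75 |
| 27.8% | 134 × 13/18 ≈ 97 | 5.775 | 0.66 |

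Keeping 134 complete participants would need 134/(16/18) = 150.75, so 151, or 134/(13/18) = 185.5, so 186.

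**4. What the 53°C limit may change.** The documents do not give the app's formula. Assume that percentages apply to the distance from the 32°C baseline. Then 140% is out of reach above 32 + (53 − 32)/1.4 = 47.0°C. In the pilot, 120% was out of reach above 32 + (50 − 32)/1.2 = 47.0°C, and two of 18 exceeded that. On this assumption the pilot implies about 11.1% loss at 140% in the main study, which is the middle row of the power table. The cold block's rate at its 0°C limit cannot be derived.

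**5. Balance between arms.** The pilot losses were 3 v 2 and 1 v 1. They are fixed by a threshold measured before training, so training cannot cause them.

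**The case against.** **The plan is not silent.** It refers to standardised procedures and a missing-data analysis, and a journal article may leave the branch above 10% to another document. This stands in part: to say the plan has no remedy would be too strong. What remains is that the article fixes the conditions for imputation, fixes them badly, and names no concrete alternative.

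**Listwise loss depends on the model.** The article does not say that all five levels, or heat and cold, enter one ANOVA. Separate t-tests by level would lose only the affected level. This stands. The power figures apply to an ANOVA spanning all heat levels, or to the 140% and 120% comparisons alone.

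**A reader might infer that early stopping by high raters in the pain arm will pull the primary contrast toward zero.** The documents do not support that reading:

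- They give no stopping rate. The study is a single session with the ISSA directly after training, and the pilot reports no withdrawals.
- A simulation with assumed inputs can produce such bias: 67 per arm, true difference 0.488 SD, correlation 0.6 between blocks, and stopping after the first block among high raters. With about 11.6% or 17.3% stopping, the complete-case difference is about 0.43 or 0.38 SD if both blocks must be complete. Analysed by modality it is about 0.46 SD in either case, a loss of 5 to 7%.
- Those who stop lose only half their ISSA ratings, so these rates are about 5.8% and 8.7% of ratings. That is under 10% if ratings are counted. Stopping is also MAR by construction, so the plan's own imputation could apply.

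Bias from stopping that differs between arms is therefore possible, but only as an assumption.

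**Conclusion.** The point holds as a defect in a stated rule. The 10% has no unit, the MAR condition cannot be verified, and no concrete method follows if either fails. On the pilot's figures the device-limit exclusion alone gives 27.8% and 11.1% by participant but 7.8% by heat cell, so whether imputation is allowed turns on an undefined denominator.

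The size is a loss of power from 0.80 to about 0.75 at 11.1% loss and 0.66 at 27.8%. This assumes listwise deletion, pilot-like rates and an unchanged effect. Both rates come from 18 people and are imprecise; 53°C may lower the heat rate, and the cold rate is unknown. The near-balanced, pre-training origin of these losses points to lost power and a sample restricted to lower thresholds. It does not show a bias between arms.

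This should be corrected before analysis, but it does not invalidate the design.

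**What to change.** In the main-study Data reduction and analytic plan:

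1. Delete the under-10% condition and the MAR/MCAR condition.
2. Analyse each primary ISSA outcome with a likelihood-based linear mixed model: group, level, modality, a random participant effect, and the pre-training pain threshold for that modality as covariate. Use every valid rating from every randomised participant who starts the ISSA, and name the covariance structure.
3. State that ratings excluded at the device limits are missing cells and do not remove the participant. Estimates at 120% and 140% then lean on the modelled threshold effect for participants who could not reach those levels, and the report should say so and give the number observed per cell.
4. Apply multiple imputation to the single-score secondary outcomes without a percentage condition.
5. Add one MNAR sensitivity analysis that shifts the missing ratings by a stated range of deltas.

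Two related passages need reconciling. The Insights section assigns five and two participants to 120% and 140% respectively, while Task evaluations gives five for 140% and two for 120%. Out-of-range targets are described as capped in the ISSA sections, whereas the analysis plan excludes the ratings.

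The cost is a rewording of a few sentences, slightly more analysis work and a covariance structure to name. SPSS has a mixed-model procedure, and no extra data or participants are needed.

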### Primary and secondary outcomes

The primary outcomes in this study are pain intensity and unpleasantness for ambiguous somatosensory sensations as assessed via the ISSA paradigm. Secondary outcomes are (i) pain-related interpretation biases for ambiguous words and scenarios as assessed via the Ambiguous Scenarios Task and Sentence Generation Task respectively, (ii) pain-related attentional and memory biases as assessed via the visual-probe task and surprise free-recall task respectively, and (iii) anxiety (State-Trait Anxiety Inventory), depression (Beck Depression Inventory-II), anxiety sensitivity (Anxiety Sensitivity Index-3), somatosensory amplification (Somatosensory Amplification Scale), pain catastrophising (Pain Catastrophising Scale), intolerance of uncertainty (Intolerance of Uncertainty Scale-12 Item), and handedness (Edinburgh Handedness Questionnaire – Short Form).

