### Procedure

The procedure for this study is shown in Fig 4. Participant ID numbers will be randomly assigned to the benign or pain modification group before data collection begins. After having read the information sheet and signed the consent form, participants will first complete the questionnaire battery. Following this, participants will complete the pain-threshold measurement task to assess their hot and cold pain thresholds. Next, participants will complete the Ambiguous Scenarios Task aiming to modify their biases towards pain-related or benign interpretations of ambiguous stimuli, according to their randomised group. Immediately following this, participants will complete the Interpretation of Ambiguous Sensation Task. All participants will then complete the battery of cognitive bias tasks. The test phase of the Ambiguous Scenarios Task will be completed first. The order of the sentence generation task and visual-probe task will be randomised and counterbalanced across participants, with the free recall memory bias task conducted last. Lastly, those randomised to the pain modification condition will complete the bias repair task. Participants will complete the study in a single session lasting approximately two hours minutes. Following completion of the study, participants will be thanked and debriefed. The entire experiment will take approximately 120 minutes to complete.

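### The pre-training pain threshold sets the uncapped ISSA temperatures, but no stated covariate rule brings it into the ISSA analysis: an inexpensive chance to gain precision is missed, though the planned test is valid

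*Protocol article*

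**What the plan says.** All references are to the Protocol article, main study unless stated.

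- **Timing (Procedure).** IDs are allocated to groups before data collection. After the questionnaires and before CBM-I, "participants will complete the pain-threshold measurement task to assess their hot and cold pain thresholds".
- **Use of the threshold (Interpretation of somatosensory sensations assessment).** "cold stimuli at 60%, 80%, 100%, 120% and 140% of an individual’s cold pain threshold will be presented three times each". Heat uses the same five percentages, as described for the pilot. Targets beyond a device limit are capped. The pilot analytic plan drops ratings where the target could not be reached, and the main study carries that processing over.
- **Outcomes (Primary and secondary outcomes).** "The primary outcomes in this study are pain intensity and unpleasantness for ambiguous somatosensory sensations as assessed via the ISSA paradigm". Interpretation bias on the Ambiguous Scenarios and Sentence Generation Tasks is listed separately, as secondary.
- **Covariates (Data reduction and analytic plan).** There are three routes:
  1. "Should any statistically significant differences be observed between groups on demographic or self-report measures, analyses will be conducted controlling for these".
  2. Age, if it correlates significantly with the ISSA ratings. The reason given is that age is related to thermal pain sensitivity.
  3. Other variables that differ between groups, in regressions of interpretation bias measures on group.
- **Descriptives (same section).** Demographics, self-report measures, cognitive bias scores and ISSA responses are listed. Thresholds and delivered temperatures are not.
- **Sample size (Participants).** "A power analysis was conducted using G*Power [82] to determine suitable sample size for an ANOVA". The inputs are f = 0.244, called medium and taken from the pilot, with power 0.80, numerator df 1 and two groups. The result is stated as: "This indicates a sample size of 134 is required for these conditions to be met". No covariate enters the calculation.

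**The concern.** The ISSA is given only after training, so the threshold is the only sensory measurement taken before it. The plan accepts thermal sensitivity as a nuisance factor when it considers adjusting for age. Yet it has no route to the direct measurement of that sensitivity, which it collects from everyone.

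The levels are relative to the individual, but the physical stimulus is not. Two people at the 100% level can receive different temperatures, reached after different ramp times at 1°C per second, and rate them on a scale anchored at no sensation. If ratings depend on threshold even after scaling, a chance difference in threshold between arms moves the group contrast. The stated descriptives would not show that difference and the stated rules would not adjust for it. Explainable variance would also stay in the error term.

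**Working it through.** **1. Does any covariate route reach the threshold in an ISSA model?**

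| Route | Variables admitted | Outcome covered | Reaches it? |
|---|---|---|---|
| 1 | Demographic or self-report measures that differ significantly | Analyses generally | No: the Self-report measures section lists questionnaires and a demographic form, without thresholds |
| 2 | Age | ISSA ratings | No: age only |
| 3 | Any variable that differs between groups | Interpretation bias measures | No: wrong outcome |

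Route 3 comes closest. However, the outcomes section, the correlation sentence in the same analytic plan and the pilot analytic plan all list interpretation bias separately from ISSA ratings.

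**2. The plan's own sample size.** Noncentral F with λ = N·f², f = 0.244, df 1 and N − 2, and α = 0.05 ("For all analyses the significance level will be set to *p* = .05 and two-tailed"). N = 133 gives power 0.7977 and N = 134 gives 0.8006. The stated 134 is reproduced. The equivalent standardised difference is d = 2f = 0.488.

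**3. Power with the threshold as covariate.** λ = N·f²/(1 − r²), df 1 and N − 3. Here r is the within-group correlation between threshold and rating. It is not in the article, so it is varied.

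| Assumed r | Power at N = 134 | N for 80% power |
|---|---|---|
| 0.1 | 0.805 | 133 |
| 0.3 | 0.836 | 122 |
| 0.5 | 0.899 | 101 |

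These are ranges under an assumption, not a corrected sample size.

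**4. Size of a chance imbalance.** Assume 67 per arm (1:1; the article does not state the ratio). The standard error of the standardised arm difference in threshold is √(2/67) = 0.173, so the 95% chance range is ±1.96 × 0.173 = ±0.34 SD. For an assumed threshold SD of 2, 3 or 4°C that is about ±0.7, ±1.0 or ±1.4°C at the 100% level.

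**5. Effect on the unadjusted contrast.** Shift = r × imbalance. At the 0.34 SD limit:

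- r = 0.1: 0.03 SD, or 7% of d = 0.488
- r = 0.3: 0.10 SD, or 21%
- r = 0.5: 0.17 SD, or 35%

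**6. Type I error.** Simulation with 40,000 runs and 67 per arm, for r = 0.3 and 0.5. Over all randomisations the unadjusted test rejects in about 4.9% of runs. In runs where the threshold imbalance fell between 0.28 and 0.40 SD, it rejects in about 7% (r = 0.3) and 12% (r = 0.5). With the covariate, the rates in those same runs are 5.0% and 5.4%.

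**7. Does one slope fit all levels?** If each target is a fixed percentage of the threshold temperature, or of its distance from the 32°C baseline, an arm difference in threshold is multiplied by 0.6 at the 60% level and by 1.4 at the 140% level. The temperature difference therefore grows with level, and a single main-effect term would not match it.

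**The case against.** The strongest reply is that the design already uses the threshold. Stimuli are scaled so that each sits at the same place relative to the individual's pain threshold, and people at the same level are meant to receive different temperatures. Scaling may remove most of the dependence of ratings on threshold. This stands: r could be near zero, and at r = 0.1 the gain is negligible.

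Second, a reader might infer that the primary contrast is biased because delivered temperature is mixed with training. The documents do not support that. Allocation is random and thresholds precede training, so the expected arm difference is zero, and chance differences are already covered by the standard error. The conditional error rates above describe uncommon trials: even an imbalance of 0.3 SD (0.3/0.173 = 1.74 standard errors) would occur in only about 8% of them.

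Third, a reader might expect the covariate to deal with capping. It does not. Capped targets equal the device limit and are not set by the threshold in the same way. Their ratings are excluded, and a covariate does not restore them.

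Fourth, covariates and baseline tables are often left to an analysis plan, and this is a condensed article. That would answer a mere omission. Here, however, the article states its covariate rules, and as written they leave out the one baseline sensory measurement. Nothing in the article forbids reporting thresholds.

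**Conclusion.** The point holds as a low-cost improvement in precision, not as correction of an invalid analysis. None of the three stated routes admits the pre-training threshold to the ISSA models, and the listed descriptives would not show an imbalance in it.

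The planned unadjusted test keeps its type I error at about 0.05, and N = 134 is correctly derived. The possible gain runs from practically nothing (power 0.805 at r = 0.1) to material (0.899 at r = 0.5).

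This rests on assumptions the article cannot settle: the correlation, the threshold SD, 1:1 allocation, and a between-group test on one rating summary, as in the sample size calculation. The pilot tables report no threshold data, so they do not fix the correlation. The absence of systematic bias also assumes that threshold measurement is unaffected by the earlier allocation of IDs. The article gives no evidence that it is affected.

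**What to change.** Add to the analytic plan that each ISSA model (intensity and unpleasantness, heat and cold) includes the participant's pre-training threshold for that modality, centred, together with its interaction with stimulus level. It should be included whatever any baseline comparison shows. A significance-triggered check on the threshold would be the weaker remedy.

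Add heat and cold thresholds, delivered temperature at each level and the number capped at each level to the descriptives, by arm.

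The cost is a sentence or two and a few table rows. The data are already collected. The group contrast loses one degree of freedom per model, and the interaction uses four more (five levels minus one) in the within-participant part. No procedure changes and no extra participants are needed. The exclusion of capped ratings remains a separate matter, which this change does not resolve.

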### Correlational analyses

Anxiety sensitivity was positively associated with unpleasantness ratings for stimuli at 60% (*r* = .51) and 80% (*r* = .51) of the pain threshold. State anxiety was positively associated with intensity ratings for stimuli at 80% (*r* = .48), and 100% (*r* = .48), of the pain threshold, as well as with unpleasantness ratings for stimuli at 60% (*r* = .72), 80% (*r* = .75) and 100% (*r* = .77) of the pain threshold. Trait anxiety was positively associated with intensity ratings for stimuli at 140% (*r* = .48) of the pain threshold, and with unpleasantness ratings for stimuli at 60% (*r* = .61), 80% (*r* = .55), 100% (*r* = .59), 120% (*r* = .56), and 140% (*r* = .54) of the pain threshold. Anxiety sensitivity was positively associated with the proportion of pain sentences generated (*r* = .57). Additionally, scores on the test phase of the Ambiguous Scenarios Task and Sentence Generation Task were correlated (*r* = .68).

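### Covariates are chosen by significance tests on the trial data, so pre-training state anxiety would usually be left out of the ISSA comparisons and an available gain in power forgone

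*Protocol article*

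**What the plan says.** All places are in the Protocol article.

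- **Demographic and self-report measures** (main study, Data reduction and analytic plan): "Should any statistically significant differences be observed between groups on demographic or self-report measures, analyses will be conducted controlling for these". The same paragraph plans regressions of the interpretation bias measures on group that control for whatever other variables differ between groups.
- **Age** (same paragraph) is first correlated with the ISSA ratings: "Should these be statistically significant, then age will be controlled for as a covariate where appropriate in the statistical analyses".
- **Significance level** (same section): "For all analyses the significance level will be set to *p* = .05 and two-tailed".
- **Sample size** (main study, Participants): a two-group ANOVA with f = 0.244, alpha 0.05, power 0.80, "numerator degrees of freedom = 1, and number of groups = 2". The result: "This indicates a sample size of 134 is required for these conditions to be met".
- **Pilot evidence** (Correlational analyses): state anxiety correlated with "unpleasantness ratings for stimuli at 60% (*r* = .72), 80% (*r* = .75) and 100% (*r* = .77) of the pain threshold", and at .48 with intensity at 80% and 100%.
- **Timing** (main study, Procedure): the questionnaires come first, before threshold testing and training. The article lists anxiety among the secondary outcomes, but on this schedule STAI-State is a baseline measure.

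No covariate is fixed in advance for the ISSA comparisons.

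**The concern.** Under randomisation a significant baseline difference is a chance event. Adjustment gains precision in proportion to how well the covariate predicts the outcome, and the between-group trigger never looks at that. Any one baseline measure therefore enters in about 5% of trials and stays out in about 95%, however prognostic it is. The age trigger does look at prognosis, but it still lets the trial data choose the model.

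Two things are at stake. The model reported for the primary outcomes depends on which baseline p-values happen to fall below .05. And precision that could be had from data already collected is mostly left unused.

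**Working it through.** **1. The plan's own figure.** With f = 0.244 (d = 2f = 0.488 for two equal groups), a noncentral F test on 1 and N − 2 df with noncentrality N·f² first reaches 80% at N = 134 (power 0.801). The stated sample size reproduces.

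**2. What the rule would have done in the pilot** (Table 2, n = 9 per arm, t on 16 df).
- STAI-State: difference 36.56 − 29.44 = 7.12; standard error √((4.59² + 11.37²)/9) = 4.09; t = 1.74, p = .10. Not adjusted.
- ASI-3 Total: difference 30.00 − 13.22 = 16.78; t = 5.13, p = .0001. Adjusted. The ASI-3 subscales give p = .010 (Social), .021 (Physical) and .003 (Cognitive).
- PCS Total p = .041, Magnification p = .048, Helplessness p = .016. Adjusted.

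The reported correlations with unpleasantness are .72, .75 and .77 for state anxiety at 60%, 80% and 100%; .54 to .61 for trait anxiety across the five levels; and .51 for anxiety sensitivity at 60% and 80%. No PCS correlation with any rating is reported. The rule would have passed over the strongest reported correlate at 60% to 100% and taken weaker ones.

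**3. Within-group correlations.** The pilot correlations pool both arms, so part of each reflects the arm difference. To remove it, for x = STAI-State and y = a rating:

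r_within = [r·√((Wx + Bx)(Wy + By)) − (n/2)·Δx·Δy] / √(Wx·Wy),

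where W = (n − 1)(s₁² + s₂²), B = (n/2)Δ² and n = 9. For unpleasantness at 80% (Table 3): Wx = 1202.8, Bx = 228.1, Wy = 3705.3, By = 1047.9, Δx = 7.12, Δy = 15.26. Then (1955.9 − 488.9)/2111.1 = .695.

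| Rating | Pooled r | Within-group r |
|---|---|---|
| Unpleasantness 60% | .72 | .66 |
| Unpleasantness 80% | .75 | .70 |
| Unpleasantness 100% | .77 | .74 |
| Intensity 80% | .48 | .38 |
| Intensity 100% | .48 | .48 |

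**4. Power at N = 134.** Always adjusting: f_adj = f/√(1 − r²), on 1 and N − 3 df. The rule was simulated as: use ANCOVA if the baseline t-test has p < .05, otherwise the unadjusted t-test (equal arms, d = 0.488, at least 40,000 trials per scenario).

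| Within-group r | Unadjusted | Stated rule (one covariate) | Always adjusted | Type I error under the rule |
|---|---|---|---|---|
| .4 | 80% | 81% | 86% | 4.6% |
| .5 | 80% | 81% | 90% | 4.4% |
| .7 | 80% | 82% | 97% | about 3.7% |

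The baseline test fired in about 5% of simulated trials. The forgone gain is roughly 5, 9 and 15 to 16 points. Always adjusting holds type I error at 5%.

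**The case against.** Several points on the other side stand.

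- **Planned power is met.** A reader might infer that the study is underpowered. It is not: at f = 0.244 the unadjusted comparison has the stated 80% and is unbiased under randomisation.
- **Error is not inflated.** A reader might infer that a data-driven model produces false positives. The one-covariate check shows the opposite, an error rate a little below 5%.
- **Not every covariate depends on a between-group test.** Age enters through its correlation with the ratings, which does address prognosis.
- **The rule would not have been idle in the pilot.** It would have adjusted for anxiety sensitivity, which is a reported correlate of unpleasantness.
- **The 97% figure is near a best case.** With n = 18 the 95% interval for r = .75 is about .44 to .90. State-anxiety correlations are reported for five of the ten pilot ratings. None is given at 120% or 140%, nor for intensity at 60%. All those reported are .48 or more, and .47 is the two-sided 5% cut-off at n = 18, so selective reporting of the larger values is possible. Cold stimuli have no pilot data. Intensity, also a primary outcome, points to r of about .4 to .5.
- **The simulation simplifies.** The actual rule tests many correlated measures, and one of those could enter and recover part of the gain.
- **Pain threshold as a compulsory covariate** is not supported. No pilot correlation with it is reported, and the stimuli are already scaled to each participant's threshold.

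None of this justifies the between-group trigger. It limits the size of the point and its severity.

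**Conclusion.** The point holds as one about an inefficient, data-dependent choice of model, not about bias or an invalid test. Pre-training state anxiety would be left out of the ISSA comparisons in about 95% of trials, although it is the strongest reported pilot correlate of unpleasantness at 60% to 100% of threshold.

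The forgone gain at N = 134 is about 5 points of power if the within-group correlation is .4, as is typical of the intensity ratings; 9 points at .5; and about 15 at .7, the upper end of what the pilot supports. This assumes that the n = 18 correlations roughly hold, equal arms, one covariate, and an effect of f = 0.244 on a single between-group comparison. The gain at 120% and 140% and for cold stimuli cannot be judged from the document.

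Severity: should be fixed; a free improvement.

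**What to change.** In the main study's Data reduction and analytic plan:

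1. State that every ISSA group comparison is adjusted for pre-training STAI-State and age, whatever the baseline comparison shows.
2. Delete both significance triggers: the between-group test for demographic and self-report measures, and the correlation test for age.
3. Delete the parallel provision that the bias-measure regressions control for variables that differ between groups. If adjustment is wanted there, name the covariates.
4. Report the unadjusted comparison as a sensitivity analysis.
5. Confirm that age is recorded. The main study's Self-report measures section does not list it among the demographic items, though eligibility (18 to 50 years) requires it to be known.

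The pre-training pain threshold may be added if the investigators have a reason, but need not be.

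The cost is wording only: STAI-State is already collected before training, and the sample size does not change. The change should be made before outcome data are examined by group.
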